
### Data Analysis

#### Quantitative Analysis

The repeated measurements (4 in total) on individuals in the 6 hubs over the three 3-month periods will be analyzed using linear mixed models. For measurement scales that are not too coarse (eg, more than 7 distinct values), the statistical analyses will make use of the REML algorithm to fit the mixed model. This algorithm will take account of missing (at-random) assessments and also allows the exploration of various autocorrelation models for the repeated measurements. Comparison of the *control* and *new program* means (adjusted for period effects) will be assessed with an *F* test. If required, after inspection of diagnostic plots of residuals and fitted values, an empirical logit transformation will be used to reanalyze any item scales that are bounded and coarse. Generalized linear mixed-model techniques will be used to analyze binomial or other categorical data. Cumulative effects of exposure to the new program on key outcome variables will also be explored using the same methods. The final analysis will be conducted after all participants have had adequate opportunity to be assessed at the end of the third period (ie, at 9 months), and the database has been locked. Process evaluation will assist in the assessment of factors that impact on the feasibility, success, and sustainability of the intervention strategies and new program. A detailed statistical analysis plan can be accessed by contacting the corresponding author.

**Table 2 table2:** Minimum effect sizes.

Key workers per hub^a,b^	Intraclass correlation^c^	Minimum detectable effect size
6	0.25	0.68
6	0.5	0.56
8	0.25	0.59
8	0.5	0.49

^a^Effect size is the expected difference between the 2 conditions (intervention-control) divided by the SD (ie, the square root of the total variance).

^b^Detectable with 80% power for the proposed stepped-wedge design with 6 hubs, 3 periods, and 4 assessment time points.

^c^Intraclass correlation: between individual variance divided by the sum of the between and within individual variances.

#### Economic Analysis

The economic analysis includes a cost analysis, together with efficiency analyses based on either of the following: (1) simple *dominance* (intervention cheaper/outcomes better or no different) or *dominated* (intervention more expensive and outcomes same or worse) and (2) more complex analyses that examine cost in relation to different definitions of value.

Simple dominance will be established using cost-effectiveness analysis that compares program costs with physical outcomes (based on primary and secondary outcomes for parents and key workers collected in the trial). The cost analyses will be conducted to determine whether the capacity building program is cheaper or more expensive than current practice, primarily from the service provider perspective but also from the perspective of parents and the health care system.

If the costs of the capacity program are not cheaper and the program is more effective, then *value* has to be analyzed to establish *value-for-money*. One way is to list the range of primary outcomes and secondary outcomes that have policy meaning to stakeholders (so called *cost-consequences analysis*) and/or express these as a series of cost-effectiveness ratios (eg, *net cost per parent satisfaction score* and *net cost per unit of staff well-being score*). A judgment call could then be made by key staff as to whether these benefits constitute sufficient return on the investment.

Another way is to place a dollar value on these outcomes to establish a return on investment using cost-benefit analysis. There are various methods available to do this (eg, value of *statistical lives* where premature death is prevented; human capital methods; and scenario-based techniques such as willingness-to-pay or conjoint analysis). A decision on the most appropriate technique, if the trial yields this result, will be made in conjunction with the service provider senior management.

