Research questions.Does the capacity building program increase:Key workers’ self-efficacy in supporting parental mental well-being (primary outcome);Managers’ self-efficacy in supporting staff and parental well-being;Parental mental well-being;Key workers’ and managers’ job-related wellbeing and mental wellbeing;Parental satisfaction with the service provided by their key worker; and/orKey workers’ and managers’ perceptions of supervisory support?Are the program and evaluation methodologies appropriate and feasible for key workers, managers, and parents?Is the program good value-for-money?Is it affordable?The cost of the capacity building program will be estimated to help determine whether this program is *value-for-money*. Simple dominance would establish this—that is, compared with current practice, is it cheaper with improved effectiveness or cost neutral with improved effectiveness. Similarly, on the flip side, if the program is dominated, then it is not value-for-money—that is, more expensive and less effective or more expensive with no improvement in effectiveness. If the program is both more expensive and more effective, then more complex tests of efficiency are required that establish value-for-money by reference to established guidelines using a metric that enables comparison across alternate uses for limited budgets (eg, a return on investment >5% and a cost per quality-adjusted life-year <AUD$50,000). Value-for-money considerations, together with affordability considerations, will inform the program’s potential to be scaled-up and adopted by other disability organizations.

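### If the program proves more effective but not cheaper, the dollar-valuation technique is chosen after that result is known, jointly with the provider's management, so the value-for-money verdict in that branch can follow the data

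*Protocol article*

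**What the plan says.** Textbox 2 (Research questions) asks whether the program is good value for money and gives a first-stage rule: "Simple dominance would establish this". It also states when the program is dominated. For a program that costs more and works better, it says that "more complex tests of efficiency are required that establish value-for-money by reference to established guidelines using a metric that enables comparison" across competing uses of limited budgets. Two benchmarks follow, introduced as examples: "a return on investment >5% and a cost per quality-adjusted life-year <AUD$50,000".

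The Economic Analysis section repeats the two stages. Its second stage opens with "If the costs of the capacity program are not cheaper and the program is more effective, then" and offers two ways forward.

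- The first is to "list the range of primary outcomes and secondary outcomes that have policy meaning to stakeholders", or to form cost-effectiveness ratios, or both. After that, "A judgment call could then be made by key staff as to whether these benefits constitute sufficient return on the investment".
- The second is to put a dollar value on the outcomes and derive a return on investment. On how to do so it says "There are various methods available to do this", names several, selects none, and closes with "A decision on the most appropriate technique, if the trial yields this result, will be made in conjunction with the service provider senior management".

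On the provider's part in the study: Setting says the study was developed with the provider, which implements the program. Phase 3 says one of its own senior managers facilitates the training. Results says the partner organization contributes cash and in-kind support.

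**The concern.** The closing sentence of Economic Analysis is a stated rule about timing and participants. It is not a detail left to a fuller plan: an analysis plan that followed it would still wait for the result before choosing the technique. Those choosing would by then know the costs and effects, and could see which techniques yield a favourable return. One party to the choice has a stake in the answer.

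Value for money is a listed research question. Textbox 2 says the answer, together with affordability, informs whether the program is scaled up and adopted by other disability organizations. Those readers need a verdict whose method did not depend on the figures it was applied to.

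**Working it through.** The article contains no economic figure to reproduce, so the check is mainly a comparison of passages, with one short calculation.

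**1. Which outcomes of the trial leave the verdict open.**

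| Result | How the verdict is reached | Fixed before results? |
|---|---|---|
| Dominant | Rule in Textbox 2 and Economic Analysis | Yes |
| Dominated | Rule in the same two places | Yes |
| More effective, not cheaper | Listing or ratios with a possible staff judgment, or cost-benefit analysis | No |

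The two sections word the edges of dominance slightly differently. For example, Textbox 2 counts cost-neutral and better as dominant, while the Economic Analysis trigger would also take that case in. Both wordings are written in advance, so this is a boundary to tidy and not part of the present point.

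**2. What the deferred choice covers.** The closing sentence follows directly on the list of monetary valuation methods: value of statistical lives, human capital, willingness to pay and conjoint analysis. Read naturally, it governs the technique within the cost-benefit route. The choice between the two routes is not fixed either, but the text gives no explicit timing for that choice or for deciding which outcomes matter to stakeholders.

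**3. Whether Textbox 2 closes the gap.** Textbox 2 requires established guidelines and a metric that permits comparison.

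- The cost-benefit route aims at a return on investment, which is one of the Textbox 2 metrics, so on that route the two sections agree.
- The listing-and-ratios route does not meet the requirement. A net cost per satisfaction or well-being score does not allow comparison across other uses of a budget, and the staff judgment has no criterion.
- Economic Analysis does not carry either benchmark forward.

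**4. Whether the 5% benchmark would fix the verdict if it were used.** With monetised benefit B and program cost C:

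- Return on investment = B/C - 1, so a return above 5% means B > 1.05 × C.
- Set C = 100 and let three techniques value the same effect at 90, 105 and 130. These values are assumed for illustration and are not in the article.
- 90/100 - 1 = -10%: benchmark failed.
- 105/100 - 1 = 5%: exactly on the line, so not above 5%.
- 130/100 - 1 = 30%: benchmark met.

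The effect and the cost are the same in all three rows, and only the technique changes. A threshold on the return therefore does not settle the verdict while the technique stays open.

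**The case against.** Several points on the other side are sound.

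- **Scope.** A reader might infer that the whole value-for-money method is chosen after the results. It is not: the dominance verdicts are set by rule, and the Abstract names cost-consequence as a secondary outcome in advance. The concern is confined to one branch and, for the quoted sentence, to one route within it.
- **Who decides.** A reader might infer that the provider alone picks the outcomes, the technique and the threshold. The text makes the technique a joint decision, the staff judgment is only something that could happen, and nothing says management selects the outcomes. The Costing section makes the service provider's perspective primary, so seeking its view is legitimate.
- **Threshold.** Two benchmarks are on paper before results. They are examples and not binding, but it would be wrong to say that no threshold was named.
- **Likelihood.** One might assume that training must cost more, which would make this the expected branch. The Costing section plans for offsets through turnover, absenteeism and revenue, and the article gives no cost figures, so that cannot be shown.
- **Multiplicity.** With many outcome scores, one might compute the chance that at least one improves by luck. That would measure how easily the branch is entered, under a rule the article does not state (that any single improved score counts as more effective). It does not measure the effect of choosing a technique late.
- **Suitability.** The right technique may depend on which outcomes change. The section itself ties statistical-life values to prevented deaths. This is a fair reason to prefer a rule for choosing over a single fixed technique, but such a rule can be written in advance.

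The defence that an article condenses a fuller plan carries little weight here, because the text itself states the deferral.

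**Conclusion.** The point holds for the branch in which the program is more effective but not cheaper. There the valuation technique is chosen once that result is known, with the management of an organization that delivers and helps fund the program. The alternative route may end in a judgment without a criterion, which does not match Textbox 2. The verdict in this branch can therefore follow the data.

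The size cannot be estimated from the article. The illustration shows only that assumed valuations of 90 to 130 per 100 of cost move the return from -10% to 30% and so across the 5% example benchmark. It rests on the assumption that the candidate techniques can differ by about that much for the same effect.

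The primary analysis of key worker confidence, the effect estimates, the costs, and the dominant and dominated verdicts are untouched. The fault lies in one conditional step of the economic evaluation, but that step answers a stated research question and is cheap to put right.

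**What to change.** Replace the closing sentence of Economic Analysis with a commitment that, before database lock and before any result by condition is released, the following are recorded in writing:

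- one base-case valuation technique, or a rule that links the technique to the outcomes that change;
- one acceptance threshold, for example the return-on-investment benchmark already in Textbox 2.

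Provider management is consulted at that stage. Other techniques are reported as sensitivity analyses. The cost-consequences table shows all primary and secondary outcomes. Staff judgments made after the results are reported as stakeholder opinion and not as the trial's verdict. There is no need to narrow the effect measure to key worker confidence, since the section deliberately draws on parent and key worker outcomes.

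If this cannot be agreed before lock, the second-stage verdict should be labelled exploratory.

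The cost is a paragraph in the economic plan and one meeting before lock. The Quantitative Analysis section already holds the final analysis until lock, so the timetable need not change. The downside is less freedom to tailor the valuation afterwards.

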#### Qualitative Analysis

The focus groups will be recorded and transcribed verbatim. Qualitative data will be analyzed and coded using an inductive, thematic approach informed by grounded theory [57]. NVivo12 software will be used to manage the data during the analysis of results [58]. Similarities and differences will be compared within and across focus groups to identify emergent themes. This will be used to generate a conceptual analysis which will be aligned with strengths and gaps in current theory, evidence, and practice to increase understanding of key issues relating to the feasibility and impact of the intervention strategies.

## Results

This study was funded in October 2014 supported by an Australian National Health and Medical Research Council Partnership Project grant (Grant number 1076861) and cash and in-kind contribution from Yooralla as the associated partner organization. This is a multiyear study, and the final year comprises the trial outlined in this study. The trial is registered with the Australian New Zealand Clinical Trials Registry (ACTRN12617001530314), retrospectively registered on 3 November 2017. Results are expected to be available by the end of 2019.

## Discussion

### Overview

Strategies to improve the mental health and well-being of parents of children with a disability are urgently needed [59] and are timely given the current rollout of the National Disability Insurance Scheme (NDIS) in Australia. The NDIS aims to improve the lives of individuals with a disability and their families. To our knowledge, there are currently no evidence-based interventions delivered within an ECIS to directly support the mental health of parents and carers of children with a disability. However, supporting mental health as well as providing child-related input is a key factor on the pathway to enabling their own, as well as their child’s, full participation in society and their community and to achieve positive health outcomes [60-62].

This study will pilot an intervention program embedded in a capacity building framework to increase ECISs’ support for the mental health of parents of children with a disability. Providing professional development about the importance of recognizing and supporting parental distress, the implications on positive child development, and the importance of seeking support for their own well-being is novel to this key worker cohort. Evidence for the effectiveness and cost of this type of intervention is lacking in the literature but is urgently needed to further understand the best models of care by staff to achieve well-being outcomes for families and children with a disability. It is anticipated that the capacity of their key worker and thus their confidence and job satisfaction may lead to improvements in their own mental well-being. The training is specifically designed to build the capacity of key workers to understand when a parent is struggling and would like to be connected with additional supports and that they are supporting an at-risk population group for poor mental health. There is a strength in providing training to all key workers to be able to identify and assist parents in the first instance of becoming aware of any psychological stress or distress as the availability of a key worker with a psychology background on each team is subject to recruitment by the service. The trainings focus on providing resources to staff and helping them to identify when the parent’s needs are out of their scope, we anticipate, will raise their awareness of when they need to refer customers to external supports. The focus of the early childhood intervention service is to aid the development of the child and to empower the family so key workers do not provide ongoing support for parental mental health but rather refer as appropriate.

On the basis of the research findings that emerged from the exploratory phase of this research, it is imperative to intervene at not only the key worker level but also to introduce and trial strategies at the organizational level to achieve sustainable change for families accessing the service for their child. A partnership between academics, clinicians, and the delivery organization allowed the development of a program that was feasible and relevant to the service that could be embedded in the service delivery system and addressed a current gap in the literature. The study design is practical and ethical for research in this space, with each hub of staff and parents exposed to the intervention by the end of the trial. A knowledge translation plan is in place to embed successful components of the program into policy documents to support the ongoing accessibility of the program for current staff and upskilling of new staff. Successful components of the intervention will be made accessible online via the staff intranet for ease of access and to allow content to be updated as new evidence of best practice arises and external support details require updating. The participatory method taken to develop and deliver the intervention is ideal for the proposed sustainability of the program, with the potential to embed within the organization’s professional development schedule. The scalability of the program is possible for other disability organizations that support parents of a child with a disability, once the trial has assessed if the intervention produces significantly improved self-efficacy and mental health for staff and parents. In addition, if service improvements and increased parent satisfaction have been shown to occur, the service will be more closely aligned with the NDIS.

### Strengths and Limitations

A strength of this study is the stepped-wedged design, which allows the collection of mixed-method data, including quantitative data, also including economic data, and qualitative data from key workers and parents, which historically are a difficult cohort to involve in longitudinal research because of family demands. Particularly, the inclusion of the economic evaluation provides a model for future studies involving service delivery organizations. The design also addresses the ethical issue of conducting a blinded randomized control trial with a vulnerable population, as we deem it inequitable to provide care for mental well-being to only a cohort of parents accessing the service. A limitation of this study is that it is conducted within a changing policy and funding context, with the NDIS roll out underway in Australia, which is having an ongoing impact to service delivery within the partner organization and which we anticipate will be a potential confounder on the outcome measurements. For organizational reasons, the first 2 hubs are not randomly selected. This is not a major issue for assessment of the impact of the program on the partnering organization as we will use both this intrahub (each hub as its own control) as well as the interhub information when estimating the effect of the new program on the organization. Incomplete randomization does, however, impact on the external validity of the program. We seek to minimize potential bias by not revealing to the staff when the new program is scheduled to be allocated to their hub, although this may become self-evident in the last 2 hubs. Owing to this research being conducted in a real-world service delivery context, there is possible contamination because of a small number of key workers working across multiple sites that will receive the intervention at varying times which may not be overcome by the methods introduced to minimize contamination impact on results. Although methods to minimize the impact of this are in place, it is possible that training at 1 site will influence their service delivery approach to parents at their alternative work place that has not yet received the intervention and other staff may observe and learn, particularly because of the transdisciplinary approach. This will be addressed through discussions with relevant key workers who will be asked to avoid talking about their learnings with staff from hubs yet to receive the intervention to minimize contamination as much as possible. A further limitation of the research was that it was not feasible to have a third group that received only the well-being materials that are provided in conjunction with the face-to-face training to assess their impact independent of the impact of the training on parental well-being.

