### Trial Design

This study employs a stepped-wedge design to evaluate the program. The design was chosen so that each hub would eventually receive the program and be provided with the new professional development opportunity. The intervention will be rolled out progressively over 9 months. The clusters for randomization will be the hubs (N=6). Randomization will be conducted by a statistician who is independent of the administration of the intervention [44]. The first 2 hubs will not be randomly selected, as senior management advised against this because of the large amount of ongoing organizational change at the service. These 2 hubs will be selected based on readiness to undergo the trial and will receive the program immediately after baseline is established with the remaining 4 hubs randomized 2 at a time, every 3 months thereafter. In this way, hubs that were previously acting as control hubs will progressively receive the program. All hubs are assessed at baseline and every 3 months thereafter. The stepped-wedge design is suitable for a phased evaluation approach such as this, in which there is an imperative to allow all participants to have access to the new program. The design also allows each hub or cluster to act as its own *pre versus post* control and, in the first 2 periods, there are at least 2 hubs acting as controls and at least 2 hubs receiving the program (Table 1). The statistical analysis (see below) will combine the *between-* and *within-* hub information on the effect of the program. We seek to minimize potential bias by not revealing to the key workers when the new program is scheduled to be allocated to their hub. However, this will be self-evident to the key workers in the last 2 hubs. Key workers that operate across multiple sites will be requested to refrain from sharing learnings or materials from the training with fellow staff at other sites who have not received the intervention. Although there is a risk of contamination, this is not anticipated to have a large effect as the number of key workers that work at multiple sites is very small.

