### Sample Size

The sample size (6 hubs) is pragmatically determined by the number of hubs at the service and the roll-out period for the intervention. We expect approximately 8 out of 10 key workers located at each hub to consent to be repeatedly assessed (at 0, 3, 6, and 9 months) following the start of the study and approximately 3 out of the 10 families that they each support to consent to be surveyed during the study. The effect of the pragmatically determined sample size on the power of the study was investigated as follows. With 6 hubs randomized 2 at a time every 3 months starting after baseline (0 months), we have a replicated (at the cluster or hub level) stepped-wedge design with 3 periods and we have made provision for between 6 and 8 key workers in each cluster to be repeatedly assessed across the periods. Accordingly, we expect to have between 144 and 192 observations of the primary outcome variable (KWC). KWC is measured on a bounded continuous outcome scale from 0 to 100. As a contingency, we assume that approximately 10% of the variance of a measurement on a randomly selected adult is *between-hub* variance and the remaining component of the variance of a randomly selected adult splits into *between* and *within* individual variance subcomponents according to either of the 2 scenarios—an *optimistic* intraclass correlation (ICC) of 0.5 or a *less optimistic* ICC of 0.25. As an example, the baseline mean for KWC may be 70, the total variance may be 18, and the variance components for hubs, individuals, and assessments within individuals may be 2, 4, and 12, respectively (ICC=0.25). We intend to use the method of restricted maximum likelihood (REML) to fit a linear mixed model to the observations of KWC. The model will have random effects terms for hubs, key workers within hubs and assessments within key workers (within hubs), and fixed effects terms for time (0, 3, 6, and 9 months, which span the three 3-month periods) and condition (control or intervention). On the basis of 2000 simulations of the trial for each of the 4 scenarios, we find that the minimum effect sizes that can be detected with 80% power range from 0.49 to 0.68 (Table 2). For each of the 4 scenarios, the minimum detectable effect size was calculated from 2000 simulations of the trial in which restricted maximum likelihood was used, in each simulation, to estimate the variance components, and an F test was used to compare the predicted means. As a contingency against an overall system improvement over time, each scenario also included an underlying trend over time (an increase of 2 units in key worker confidence (KWC) from the first to the last assessment). Simulations assumed baseline KWC=70, total variance=18, and between-hubs variance=2 (11.1% of the total variance) with a corresponding coefficient of variation (CV)=6.1%. Simulations were also repeated with total variance=49 and between-hubs variance=5 (10.2% of the total variance) with a corresponding CV=10%. As expected, the minimum detectable effect sizes (not shown) were very similar—a consequence of standardizing the effect difference by the square root of the total variance. Accordingly, we conclude that this study has moderate-to-high power to detect moderate effect sizes for outcome variables that are measured repeatedly on key workers.

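### Choosing the first two hubs on readiness is a threat to internal validity, not only to generalizability, and the between-hub information cited as reassurance is what carries a level gap into the estimate; the likely bias is modest

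*Protocol article*

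**What the plan says.** Trial Design (protocol article) states that "The first 2 hubs will not be randomly selected" and gives the criterion: "These 2 hubs will be selected based on readiness to undergo the trial". Senior management asked for this because of continuing organizational change. The randomized part is the "remaining 4 hubs randomized 2 at a time, every 3 months thereafter".

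Sample Size describes the allocation differently: "With 6 hubs randomized 2 at a time every 3 months starting after baseline (0 months". It also sets out the model: "The model will have random effects terms for hubs, key workers within hubs and assessments within key workers (within hubs", with "fixed effects terms for time (0, 3, 6, and 9 months, which span the three 3-month periods) and condition (control or intervention". There is no fixed term for hub or for start sequence.

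Strengths and Limitations discloses the non-random start but treats it as minor for judging the program's effect on the partner organization, because "we will use both this intrahub (each hub as its own control) as well as the interhub information" when estimating the effect. The only consequence it names is "Incomplete randomization does, however, impact on the external validity of the program".

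**The concern.** Readiness decides which hubs are treated first and longest. If readiness is related to the level of key worker confidence (KWC), or to its course over time, then condition and hub are confounded. That affects whether the estimate is right for these six hubs, which is internal validity.

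The stated reassurance also points partly the wrong way. The within-hub comparison does protect against a stable difference between hubs. The between-hub comparison does not: a random hub effect assumes that hub level is unrelated to start time, and choosing the ready hubs first may break that assumption. A reader who relies on this paragraph would take the estimate as safe for the organization, which the design does not guarantee.

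**Working it through.** **Inputs.** From Table 1: six hubs, assessments at 0, 3, 6 and 9 months, with hubs 1-2, 3-4 and 5-6 first under intervention at months 3, 6 and 9. From Sample Size: 6 or 8 key workers per hub; total variance 18 (SD = √18 = 4.24); variance components for hub, individual and assessment of 2, 4, 12 (ICC 0.25). The ICC 0.5 split, 2, 8, 8, is derived. Assumed, because not stated: two-sided alpha of 0.05.

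**Method.** Generalized least squares for the stated model, with fixed time and condition and covariance V built from the components. The condition row of (X'V⁻¹X)⁻¹X'V⁻¹ gives the weight of each hub-by-time mean, and the matching diagonal element of (X'V⁻¹X)⁻¹ gives SE². Minimum detectable effect size: MDES = (1.960 + 0.842) × SE / √18. With hub fixed, SE² = 0.6 × (assessment variance / key workers per hub).

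**Reproducing Table 2.** For 6 workers and ICC 0.25, SE = 1.047, so MDES = 2.802 × 1.047 / 4.243 = 0.69 (stated 0.68). All four scenarios agree within 3%.

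**Weights, 6 workers, ICC 0.25.** For each of hubs 1 and 2, at months 0, 3, 6 and 9:
- random hubs: -0.115, 0.250, 0.067, -0.115. The sum over both hubs is 0.173; over months 3-9 only, 0.404.
- fixed hubs: -0.150, 0.250, 0.050, -0.150. The sum is 0; over months 3-9 only, 2 × 0.150 = 0.30.

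The first sum is the share of a constant gap that becomes bias. The second is the share of a lasting shift that begins by month 3. Month 3 carries the largest weight for these two hubs, and there they are the only treated hubs, so that contrast is wholly non-randomized.

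| Workers / ICC | Table 2 MDES | MDES, random hubs | MDES, fixed hubs | Share of constant gap, random (fixed) | Share of shift from month 3, random (fixed) |
|---|---|---|---|---|---|
| 6 / 0.25 | 0.68 | 0.69 | 0.72 | 0.173 (0) | 0.40 (0.30) |
| 6 / 0.5 | 0.56 | 0.575 | 0.59 | 0.103 (0) | 0.36 (0.30) |
| 8 / 0.25 | 0.59 | 0.60 | 0.63 | 0.145 (0) | 0.39 (0.30) |
| 8 / 0.5 | 0.49 | 0.50 | 0.51 | 0.088 (0) | 0.35 (0.30) |

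**Size of a level bias, variances as planned.** A gap of one between-hub SD is √2 = 1.41 units. Largest: 0.173 × 1.41 = 0.24 units, /4.24 = 0.06 SD. Smallest: 0.088 × 1.41 = 0.12 units, or 0.03 SD.

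**Size with variances estimated by REML.** A large gap raises the estimated hub variance, which down-weights between-hub information. In 1000 null simulations per cell, gaps of 1.41, 2.83 and 4.24 units gave mean bias of 0.28, 0.30 and 0.31 units (6 / 0.25) and 0.13, 0.20 and 0.20 units (8 / 0.5), so at most 0.31 / 4.24 = 0.07 SD. A second set of 600 runs per cell at 4.24 units gave 0.09, 0.05, 0.07 and 0.04 SD in Table 2 order. Null rejection was 6-8.5% with a gap, against 4-7% without. In a single trial where the hub variance is estimated near zero, the share rises to 0.21-0.41.

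**Size of a shift from month 3.** As an illustration only, suppose hubs 1-2 alone gain 2 units for other reasons. Random hubs: 0.35 to 0.40 × 2 = 0.7 to 0.8 units, about 0.17-0.19 SD. Fixed hubs: 0.30 × 2 = 0.6 units, about 0.14 SD. A linear differential trend does little: -0.02 to +0.03 per unit of total change with random hubs, -0.07 with fixed hubs.

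**Four randomized hubs alone.** MDES 1.05, 0.87, 0.91, 0.75 with random hubs; 1.08, 0.88, 0.93, 0.76 with fixed hubs.

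**The case against.** The case for leaving the text alone has weight. Non-random selection is disclosed in Trial Design, in the title of Table 1 and in the limitations. The limitations paragraph puts each hub as its own control first, and by the weights above 83-91% of a constant gap is already removed under the random-hub model. All hubs have a baseline assessment, so a starting gap would be visible. The article refers to a detailed statistical analysis plan, which may hold sensitivity analyses; their absence here is not a fault.

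Most of this stands and limits the size of the point. It does not rescue the reasoning: what is left of a level gap enters through the between-hub information, and an unseen plan cannot make external validity the only consequence.

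Three stronger readings are tempting and not supported:
- A reader might infer that the program would look effective even if it did nothing. The document ties readiness to organizational change, not to confidence, so both the link and its sign are assumptions, and the simulated rise in false positives is small.
- A reader might scale the 9-17% to a bias of 0.09-0.17 SD for a gap of one total SD. Such a gap is 4.24 / 1.41 = 3 between-hub SDs, and the figure holds the hub variance at 2, whereas the planned REML fit estimates it and roughly halves the bias.
- A reader might infer that fixed hub effects cure the problem. They remove the level part only, and do slightly worse under a linear differential trend.

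**Conclusion.** The statement in Strengths and Limitations is wrong as it stands: selection on readiness is a potential internal-validity problem, and between-hub information is not a safeguard against it. For a constant level gap the bias is modest: 0.03-0.06 SD for one between-hub SD with the planned variances, and on average below about 0.1 SD under REML even for one total SD, against an MDES of 0.49-0.68. The larger exposure is a non-program change in the first two hubs from month 3, of which 35-40% enters with random hubs and 30% with fixed hubs. The document makes such a change conceivable, since it reports ongoing organizational change and expects the national scheme's roll-out to be a potential confounder, but it gives no size. All of this is conditional on readiness being related to confidence or its course, and on the protocol's example variance components. Severity is moderate: the reasoning and wording need correcting, but the design is not invalidated.

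**What to change.** 1. In Strengths and Limitations, remove the reassurance that the non-random start matters little, and name selection on readiness as a threat to internal validity, including differential change over time. External validity can stay as a further consequence.
2. Fit hub as a fixed effect in the primary model, or at least in a pre-specified sensitivity analysis. This removes the level bias. The cost is one model run and an MDES 2-5% larger (for example 0.69 to 0.72, or 0.50 to 0.51).
3. Report the four randomized hubs alone as a check, and say that it is imprecise (MDES about 0.75-1.08). It is the only one of these analyses free of a shift confined to the first two hubs.
4. Reconcile Sample Size, which describes all six hubs as randomized, with Trial Design, where four of six are. This is wording only; the Table 2 figures depend on the layout and reproduce.
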